## 2. OBJECTIVES

### Primary Objective:

- To determine the acute and chronic effects of pure epicatechin and quercetin-3-glucoside on vascular and endothelial function – as measured by Flow-Mediated Dilation.

### Secondary Objectives:

- To determine the acute and chronic effects of pure epicatechin and quercetin-3-glucoside on additional functional markers of vascular function – as measured by blood pressure, pulse wave velocity, pulse wave analysis and vasomotion.
- To determine the acute and chronic effects of pure epicatechin and quercetin-3-glucoside on biomarkers of vascular function (e.g. plasma nitric oxide levels, endothelin-1 and ADMA).
- To determine the acute and chronic effects of pure epicatechin and quercetin-3-glucoside on biomarkers of endothelial function (e.g. sVCAM-1, sICAM-1 and sE-selectin).
- To determine the acute and chronic effects of pure epicatechin and quercetin-3-glucoside on biomarkers of inflammation (e.g. IL-6, IL-8 and TNF- $\alpha$ ).
- To determine the effects of pure epicatechin and quercetin-3-glucoside on markers of renal function by estimation of glomerular filtration rate (eGFR).
- To determine the effects of epicatechin and quercetin-3-glucoside intake on gene expression using peripheral blood mononuclear cells (PBMCs).
- To compare the effects of pure epicatechin and epicatechin in cocoa on FMD.

### 3. STUDY DESIGN

#### Part 1 (Supplement Study):

The study will be undertaken as a three-armed, placebo-controlled, double-blind, cross-over trial. At the start of the study, participants will be asked to follow a 1-week run-in period during which they will be given dietary advice to avoid the consumption of flavonoid-rich foods. Upon completion of the run-in period, participants will follow three 4-week intervention periods with each intervention arm separated by a 4-week washout period. Four weeks after completion of the last intervention arm, participants will be asked to return to the university on two different mornings – separated by two weeks. Measurements of vascular and endothelial function will be taken before and two hours after consumption of either a high or a low-flavanol cocoa beverage. These measurements will serve purely as a positive control for Flow-Mediated Dilation.

Those interested in taking part in the study will first be asked to attend an information session, during which the study will be explained and preliminary blood pressure measurements will be taken. Those deemed eligible based on the blood pressure measurements will be invited to a screening session. During the screening session blood samples will be taken, blood pressure, height, weight and waist circumference will be measured and participants will be asked to complete a short medical history and lifestyle questionnaire. Blood samples taken during the screening will be used to analyse biochemical parameters mentioned in the inclusion criteria (see chapter 4.2). Based on the results of the screening session, those deemed eligible will be asked to take part in the study – which will start with a one-week run-in period. During the one week run-in period, participants will be given dietary guidelines to restrict the consumption of certain flavonoid-rich foods (see Appendix I). This dietary advice will be maintained throughout the study period.

Forty pre-hypertensive subjects will be sequentially randomised to one of the three intervention arms depending on their allocated treatment sequence (see table 5.1). For the three treatments, subjects will be asked to ingest either 160mg of quercetin-3-glucoside (QUER), 100mg of epicatechin (EPI) or placebo capsules (PLA) per day. Supplements will be provided in the form of capsules which will be ingested twice daily – at lunch and in the evening with dinner and with a glass of water.

Baseline measurements will be taken on the first morning of each intervention arm, following an overnight fast ( $T_0$ ). Hereafter, participants will be asked to consume two capsules per day for four weeks. After the four-week intervention period, follow-up measurements will be taken

at the same time of day as the baseline measurements, again following an overnight fast ( $T_1$ ). This will be done in order to determine the chronic effects of pure flavonoid consumption. Following these follow-up measurements, participants will be asked to consume two final capsules (i.e. the daily dose). Two hours after consumption of these capsules, additional measurements will be taken in order to determine the acute effects of flavonoid supplementation ( $T_A$ ). Changes in values between  $T_0$  and  $T_1$  will allow the analysis of the chronic effects of the intervention as compared to placebo over the 4-week period while  $T_0$  and  $T_A$  will allow analysis of the acute effects during a 2-hour timeframe. For an overview of the timeline of the intervention period and the measurements to be taken, please refer to figure 3.1 and table 3.1.

Participants will be asked to collect 24-hour urine samples during the 24-hour period preceding the baseline and follow-up measurements (6 collections in total). This will be done in order to measure compliance. In addition, 24-hour ambulatory blood pressure measurements will be taken during the 24-hour period preceding baseline and follow-up measurements.

Halfway between each intervention period (i.e. two weeks after the start of each intervention/washout period) participants will be asked to revisit the university ( $T_{1/2}$ ). During these visits, participants will be weighed and a blood sample will be taken. These measurements will be taken at the same time of day as the baseline and follow-up measurements and will last no more than 15 minutes.

Two days prior to the follow-up measurements, participants will be asked to come to the university in order to collect a standardised meal as well as materials for urine collection and 24-hour ambulatory blood pressure monitors. The standardised meal will be consumed the evening prior to the baseline and follow-up measurements.

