## 5. TREATMENT OF SUBJECTS

### 5.1 Investigational product/treatment

The three intervention arms (QUER, EPI, and PLA) will each use different investigational products. During the QUER intervention, participants will be required to take supplements of quercetin-3-glucoside (160mg/d) in the form of capsules. Epicatechin supplements (100mg/d), also in the form of capsules, will be provided during the EPI intervention arm. These dosages are based on three times the 90th percentile of epicatechin and quercetin intake [20, 40]. Finally, capsules containing microcrystal cellulose and 1% colloidal siliciumdioxide will be used as placebo capsules. The flavonoid capsules will also contain microcrystal cellulose as an excipient. To prevent differentiation in appearance, the placebo capsules will be produced by the same company where the flavonoid capsules will be made (*Het Gelre Apotheek, Apeldoorn*). All supplements will be encapsulated in non-transparent capsules and will be matched for appearance and size (capsule size “0”). During the 4-week intervention period, two capsules will be consumed per day - one at the lunch and the second in the evening before dinner. Participants will be asked to consume the capsules with a meal and a glass of water.

Two hours after the follow-up measurements, participants will be asked to consume two additional capsules with a glass of water. This will be done to determine the acute effects of flavonoid supplementation on markers of cardiovascular health.

Four weeks after completion of the last intervention arm, participants will be asked to return to the university on two different mornings – separated by two weeks. Measurements of vascular and endothelial function will be taken before and two hours after consumption of either a high or a low-flavanol cocoa beverage. Consumption of the low or high-flavanol cocoa will be randomly assigned. The high-flavanol cocoa beverage will be matched such that it provides the same amount of epicatechin as the daily dose of epicatechin during the intervention (i.e. 100mg).

During the study, participants will be provided with a list of high-flavonoid containing foods (see Appendix I). They will be asked to avoid over-consumption of such food products during the intervention period. Specifically, participants will be asked to consume no more than 1 cup of tea or glass of red wine per day and to avoid the consumption of chocolate, apples and onion soup.

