## 8. STATISTICAL ANALYSIS

Statistical analyses will be conducted based on the intention-to-treat principle. An additional per-protocol analysis will be conducted, however, the intention-to-treat analysis will remain leading. Researchers involved in the statistical analysis will remain blinded to treatment allocation. For statistical significance, a two-tailed p-value of 0.05 will be set.

All data collected during the study will be quantitative. Continuous variables will be expressed as means  $\pm$  standard deviation while categorical variables will be expressed in frequencies. Data will be tested for normality by visual inspection of Q-Q plots and histograms.

Basic descriptive analyses (including age, gender, BMI and blood pressure) will be carried out based on subject characteristics obtained during the screening and baseline measurements.

A repeated measures analysis of variance (ANOVA) will be conducted to compare differences in intraindividual responses to the treatments. Changes from  $T_0$  to  $T_1$  will be used to determine the chronic effect of the intervention. Changes from  $T_1$  to  $T_A$  will be used to determine the acute effects of the intervention. Additional paired t-tests will be carried out to compare baseline values ( $T_0$ ) of outcome measures.

For data that are not normally distributed, a nonparametric Friedman's rank test will be conducted. All statistical analyses will be carried out using the SPSS 19.0 or SAS 9.2 software packages.

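### Section 3 takes the acute effect from T0 to TA, an interval of four weeks plus two hours that also contains the chronic effect; it should be T1 to TA, as in Section 8

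*Protocol*

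**What the plan says.** The primary objective covers two effects on flow-mediated dilation (FMD): "To determine the acute and chronic effects of pure epicatechin and quercetin-3-glucoside on vascular and endothelial function".

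Section 3, Part 1, sets the clock within each arm:

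- T0: "Baseline measurements will be taken on the first morning of each intervention arm, following an overnight fast".
- Between T0 and T1: "participants will be asked to consume two capsules per day for four weeks".
- T1: fasting follow-up at the end of the four weeks.
- TA: two hours after two final capsules, which are taken once the T1 measurements are done.

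The same section then assigns the contrasts. For the chronic effect it names the change between T0 and T1, which "will allow the analysis of the chronic effects of the intervention as compared to placebo over the 4-week period". For the acute effect it pairs T0 with TA instead, a comparison that "will allow analysis of the acute effects during a 2-hour timeframe".

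Section 8 agrees on the chronic contrast: the change from T0 to T1 "will be used to determine the chronic effect of the intervention". It differs on the acute one: the change from T1 to TA "will be used to determine the acute effects of the intervention".

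**The concern.** T0 and TA are not two hours apart. A contrast between them picks up whatever four weeks of daily capsules have done, as well as anything the final dose does. Reported as an acute effect, it would credit the last dose with a response that may have built up over the whole period. The acute effect on FMD is named in the primary objective, so the protocol should not carry a wrong definition of it. FMD is measured at T0, T1 and TA, so either contrast can be computed, and the data collection itself will not expose the error.

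**Working it through.** **The identity.** For any outcome measured at all three times,

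TA − T0 = (T1 − T0) + (TA − T1).

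The first bracket is the chronic contrast of both Section 3 and Section 8. The second is the acute contrast of Section 8. The Section 3 acute contrast is therefore the sum of the two. This is algebra and needs no assumption.

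**Placebo does not cancel it.** Taking active minus placebo on both sides leaves the placebo-corrected chronic effect in the sum, because the placebo arm has no chronic flavonoid effect to subtract.

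**Inputs, all from Section 4.4.** The SD of the treatment response is 2.7. The chronic effect is 1.3 FMD points, taken from cocoa studies. The planning formula is n = 7.9 × (SD/D)². It returns 7.9 × (2.7/1.3)² = 34.1, rounded up to the stated 35, so these inputs are the ones the plan used for the chronic effect.

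**Illustration: chronic effect 1.3, acute effect 0.**

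- T1 to TA: expected contrast 0.
- T0 to TA: expected contrast 1.3 + 0 = 1.3 points.

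**How often that would be declared significant.** This uses a two-sided 0.05 test as in Section 8 and a normal approximation, and assumes that the SD of 2.7 applies to the contrast.

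| n | Standard error | 1.3 / SE | P(significant), T0 to TA | P(significant), T1 to TA |
|---|---|---|---|---|
| 35 | 2.7/√35 = 0.456 | 2.85 | Φ(2.85 − 1.96) = 0.81 | 0.05 |
| 40 | 2.7/√40 = 0.427 | 3.04 | Φ(3.04 − 1.96) = 0.86 | 0.05 |

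With half the chronic effect (0.65 points), the T0-to-TA figures are 0.30 and 0.33.

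**Which passage is wrong.** Four places bear on the interval besides Section 3:

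| Place | What it describes | Fits |
|---|---|---|
| Section 8 | Acute change from T1 to TA | T1 to TA |
| Summary | Measurements either side of the dose on the last day of each intervention | T1 to TA |
| Section 6.2, Part 1 | Capsules after the T1 measurements, TA two hours after intake | T1 to TA |
| Section 6.4.3, compliance | Plasma sampled before the final supplement and two hours after it | T1 to TA |

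Section 3's own mention of two hours also fits T1 to TA and cannot fit T0 to TA.

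**EID.** Table 3.1 and Section 6.4.1 both schedule EID in Part 1 at T0 and TA, but not at T1. Section 6.2 says that T1 repeats the baseline measurements, yet its list of them does not name EID. On this schedule T1 to TA cannot be computed for EID; only the combined contrast can.

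**Capsule timing.** Section 5.1 says: "Two hours after the follow-up measurements, participants will be asked to consume two additional capsules with a glass of water". Sections 3 and 6.2 have the capsules taken after the T1 measurements, with the two hours running from intake to TA. In one account the two hours precede intake; in the other they follow it.

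**The case against.** The strongest reply is that Section 8 is the section that fixes the statistical contrasts and it is unambiguous. An analyst working from it would never compute T0 to TA, and Section 3 looks like a slip of one subscript in a design narrative. That stands, and it limits the practical risk. It does not make the sentence in Section 3 correct.

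A reader might go further than the documents allow in three ways.

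- **That two equally live definitions compete and the trial's primary answer hangs on the choice.** Every other passage that bears on the interval points to T1 to TA. The main study parameter (Section 6.1.1) is the FMD change across the intervention period and does not name the acute contrast. The enrolled number of 40 comes from the chronic calculation, and both sections define the chronic contrast alike.
- **That the spurious 1.3 points should be set against the 1.5-point acute effect in Section 4.4 and called most of the expected acute effect.** Section 4.4 gives 1.5 for the cocoa intervention. The protocol states no separate acute effect for the capsules, so that ratio compares unlike quantities.
- **That rewording Section 3 settles every acute outcome.** It does so for FMD, but not for EID, which has no T1 measurement.

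The capsule-timing discrepancy is a separate matter and does not bear on whether T0 or T1 is the reference. Figure 3.1, which Section 3 cites for the timeline, is not available in the text reviewed, so whether it clarifies the clock could not be checked.

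**Conclusion.** The point holds as an error in Section 3. The stated acute contrast spans four weeks plus two hours and equals the chronic effect plus the acute effect. Section 8 has the interval that matches a two-hour effect.

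The size is conditional on Section 3 being followed. With a chronic effect of 1.3 points and no acute effect, 1.3 points would be reported as acute, and with 35 to 40 subjects this would reach significance about 81% to 86% of the time. Those figures illustrate the consequence and do not estimate an expected bias: they rest on a cocoa-derived effect, an acute effect of exactly zero, an SD of 2.7 for the T0-to-TA contrast and a normal approximation.

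**What to change.** 1. Amend Section 3 so that the acute effect is the change from T1 to TA, active versus placebo, as in Section 8. Describe it as the acute effect after four weeks of supplementation, since T1 is not an unexposed baseline in the active arms.
2. State that EID, scheduled at T0 and TA but not at T1, yields only a combined chronic-plus-acute contrast and must not be reported as an acute effect.
3. Separately, reconcile the capsule timing in Section 5.1 with Sections 3 and 6.2, so that a single clock links T1, intake and TA.

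The cost is a wording amendment. No new FMD measurement is needed, and the sample size and the chronic analysis stay as they are. The price of leaving the EID schedule unchanged is that no purely acute EID contrast will be available.

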### Part 2 (Cocoa Study):

Four weeks after completion of the last intervention arm, participants will be asked to take part in Part 2 of the study. Part 2 will be optional and participation will not be obligatory for the participants. Those who opt to take part in Part 2 will be asked to return to the university on two different mornings – separated by two weeks. Measurements of vascular and endothelial function will be taken before and two hours after consumption of either a high or a low-flavanol cocoa beverage. These measurements will be used to compare the effects of pure epicatechin and epicatechin in cocoa on FMD and will also serve as positive control for FMD. For these measurements, blood samples will also be taken for analysis of nitric oxide and plasma flavonoid concentrations.

[figure not shown]

Figure 3.1. Schematic overview of intervention plan and points of measurements. Time times used here are only used as an example.

Table 3.1. Measurements to be taken during the FLAVO-studie.

| Measurement                                       | Specimen | Screening | T 0 | T A | T ½ | T 1 | T 2 & T 3 |
|---------------------------------------------------|----------|-----------|----------------|----------------|----------------|----------------|---------------------------------|
| Anthropometrics                     |          |           |                |                |                |                |                                 |
| Height                                            | N/A      | X         |                |                |                |                |                                 |
| Weight                                            | N/A      | X         | X              | X              | X              | X              | X                               |
| Macrovascular Function Markers      |          |           |                |                |                |                |                                 |
| Blood Pressure (systolic, diastolic and central)  | N/A      | X         | X              | X              |                | X              | X                               |
| 24-hour Ambulatory Blood Pressure                 | N/A      |           | X              |                |                | X              |                                 |
| Heart Rate                                        | N/A      | X         | X              |                |                | X              |                                 |
| Flow Mediated Dilation                            | N/A      |           | X              | X              |                | X              | X                               |
| Endothelium-Independent Dilation                  | N/A      |           | X              | X              |                |                | X                               |
| Microvascular vasomotion                          | N/A      |           | X              | X              |                | X              | X                               |
| Pulse Wave Analysis (PWA)                         | N/A      |           | X              |                |                | X              |                                 |
| Pulse Wave Velocity (PWV)                         | N/A      |           | X              |                |                | X              |                                 |
| Biomarkers of Vascular Function     |          |           |                |                |                |                |                                 |
| Nitric Oxide (NOx)                                | Plasma   |           | X              | X              |                | X              | X                               |
| Endothelin-1                                      | Plasma   |           | X              | X              |                | X              |                                 |
| Asymmetric Dimethylarginine (ADMA)                | Plasma   |           | X              | X              |                | X              |                                 |
| Biomarkers of Endothelial           |          |           |                |                |                |                |                                 |
| sVCAM-1 & sICAM-1                                 | Plasma   |           | X              |                |                | X              |                                 |
| sE-selectin                                       | Plasma   |           | X              |                |                | X              |                                 |
| Soluble Thrombomodulin                            | Plasma   |           | X              |                |                | X              |                                 |
| Von Willebrand Factor                             | Plasma   |           | X              |                |                | X              |                                 |
| Biomarkers of Inflammation          |          |           |                |                |                |                |                                 |
| C-Reactive Protein                                | Plasma   |           | X              |                |                | X              |                                 |
| Serum Amyloid A                                   | Plasma   |           | X              |                |                | X              |                                 |
| Interleukin-6                                     | Plasma   |           | X              |                |                | X              |                                 |
| Interleukin-8                                     | Plasma   |           | X              |                |                | X              |                                 |
| Tumor Necrosis Factor-α                           | Plasma   |           | X              |                |                | X              |                                 |
| Monocyte Chemoattractant Protein -1               | Plasma   |           | X              |                |                | X              |                                 |
| Biomarkers of Compliance            |          |           |                |                |                |                |                                 |
| Plasma Concentrations Epicatechin and Quercetin   | Plasma   |           | X              | X              | X              | X              | X                               |
| Excreted Epicatechin and Quercetin                | Urine    |           | X              |                |                | X              |                                 |
| Markers of Renal Function           |          |           |                |                |                |                |                                 |
| Estimated Glomerular Filtration Rate (Creatinine) | Plasma   |           | X              |                |                | X              |                                 |
| Other                               |          |           |                |                |                |                |                                 |
| Glucose & Insulin                                 | Plasma   |           | X              |                |                | X              |                                 |
| Hb A1C and blood cell count                       | Plasma   |           | X              |                |                | X              |                                 |
| Lipids and lipoproteins                           | Plasma   |           | X              |                |                | X              |                                 |
| Peripheral Blood Mononuclear Cell Gene Expression | N/A      |           | X              |                |                | X              |                                 |
| Blood safety parameters (ALAT, ASAT, γ-GT, ALP)   | Plasma   | X         | X              | X              | X              | X              | X                               |
| Protein and albumin excretion                     | Urine    | X         | X              |                |                | X              |                                 |

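### The secondary comparison of pure epicatechin with cocoa epicatechin on FMD is not like for like: one is tested after four weeks of daily epicatechin, the other as a single drink off supplement

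*Protocol*

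**What the plan says.** The last secondary objective in Section 2 is "To compare the effects of pure epicatechin and epicatechin in cocoa on FMD". Section 3 (Part 2) says of the cocoa visits: "These measurements will be used to compare the effects of pure epicatechin and epicatechin in cocoa on FMD". The Summary and Section 6.2 give the same use of the cocoa data, and all three add a role as positive control. Two places say otherwise. Section 3, Part 1, states: "These measurements will serve purely as a positive control for Flow-Mediated Dilation". Section 1 also limits the cocoa drink to that role.

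For pure epicatechin, Section 3 (Part 1) has baseline measurements at T0 and then: "Hereafter, participants will be asked to consume two capsules per day for four weeks". The T1 measurements follow. The full daily dose is then taken in one go, and TA is measured two hours later. Two definitions of the acute change are given:

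- Section 3 (Part 1) says that T0 and TA "will allow analysis of the acute effects during a 2-hour timeframe".
- Section 8 says that changes from T1 to TA "will be used to determine the acute effects of the intervention".

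For cocoa, Part 2 starts four weeks after the last arm. It has two visits two weeks apart, each with one drink and measurements before and two hours after. Section 5.1 assigns the high- or low-flavanol drink at random and matches the high-flavanol drink to 100 mg epicatechin. The six randomised sequences in Section 6.3 contain only placebo, epicatechin and quercetin. On participation: "Part 2 will be optional and participation will not be obligatory for the participants".

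**The concern.** A comparison of two sources of one compound should differ only in the source. Here the recent exposure differs as well. The pure-epicatechin reading is taken in people who have had the compound daily for four weeks, and the cocoa reading in people who have been off it for at least four weeks. If four weeks of epicatechin changes FMD, which is what the chronic part of the primary objective tests, that change either enters the pure-epicatechin acute figure or alters the room left for it. An apparent difference between capsule and cocoa, or the absence of one, could then be a product of the schedule. A statistical analysis plan can define the contrast, but it cannot make the two exposures alike.

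**Working it through.** **Exposure side by side**

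| | Pure epicatechin | Cocoa epicatechin |
|---|---|---|
| Dose before the reading | 100 mg | 100 mg |
| Time of reading | 2 h | 2 h |
| Preceding state | four weeks of daily epicatechin | off epicatechin for at least four weeks |
| Control | placebo capsules | low-flavanol cocoa |
| In the Section 6.3 sequences | yes | no |

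Time off epicatechin at the first cocoa visit depends on the sequence. Arms occupy weeks 0–4, 8–12 and 16–20, and Part 2 starts at week 24. The gap is therefore 24 − 20 = 4, 24 − 12 = 12 or 24 − 4 = 20 weeks.

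**The protocol's own figures**

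Section 4.4 gives an SD of response of 2.7, an acute cocoa effect of 1.5, a chronic effect of 1.3, and n = 7.9 × (SD/D)². I read these as percentage points of FMD.

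- Acute: 7.9 × (2.7/1.5)² = 25.6 (stated 25).
- Chronic: 7.9 × (2.7/1.3)² = 34.1 (stated 35).

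Both are reproduced to within one subject. No figure is given for the pure-versus-cocoa comparison.

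**Apparent source difference when there is none**

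Assume that both sources have the same true single-dose effect of 1.5, that four weeks of epicatechin adds 1.3, and that a share f of this chronic gain displaces the acute increment. The documents do not give f, so the range is 0 to 1.

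- T1 to TA, pure: 1.5 − 1.3f. Minus cocoa (1.5): −1.3f.
- T0 to TA, pure: 1.3 + (1.5 − 1.3f) = 2.8 − 1.3f. Minus cocoa (1.5): 1.3 × (1 − f).

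| f | T1 to TA, pure minus cocoa | T0 to TA, pure minus cocoa |
|---|---|---|
| 0 | 1.50 − 1.50 = 0 | 2.80 − 1.50 = +1.30 |
| 0.5 | 0.85 − 1.50 = −0.65 | 2.15 − 1.50 = +0.65 |
| 1 | 0.20 − 1.50 = −1.30 | 1.50 − 1.50 = 0 |

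Neither definition gives zero across the whole range, and they err in opposite directions.

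**Would such a difference be noticed?**

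Take the control-corrected double difference in the same people, with SD 2.7 for each corrected effect and correlation ρ between them. Its SD is 2.7 × √(2(1 − ρ)), which is 3.82 at ρ = 0 and 2.70 at ρ = 0.5. With 20 to 36 participants, two-sided 0.05 and a normal approximation, a spurious 1.3-point difference would be declared significant in about 33% (n = 20, ρ = 0) to 82% (n = 36, ρ = 0.5) of trials. For 0.65 points the range is about 12% to 30%. The correlation and the Part 2 numbers are assumptions.

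**The case against.** Much of the case on the other side stands.

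- **Order and self-selection.** A reader might infer that cocoa coming last and optional participation also bias the source contrast. The documents do not support that as a main charge. Each product has its own control, so correcting each response by its control removes an additive time shift. Part 2 subjects all come from Part 1, so the contrast can be made within person. What remains is a possible treatment-by-time interaction and limited generalisability.
- **Raw comparison or equivalence claim.** The protocol plans neither. Section 8 does not describe this contrast, but that detail may be in an analysis plan that is not shown.
- **Direction.** It is tempting to say that the design favours cocoa by up to 1.3 points. That needs both full overlap and T1 to TA. With no overlap, T1 to TA shows no bias. Under T0 to TA, any bias favours pure epicatechin.
- **Precision.** A reader might say that the confidence interval must exceed either assumed effect. With 27 completers (30 less 10%) and independence, the half-width is about ±1.51. It is about ±1.29 with 36 subjects and independence, and about ±1.07 with 27 subjects and ρ = 0.5. The statement holds only in the first case, and there barely. Low power for a secondary contrast is not in itself an error.
- **T0 as a slip.** Section 3 may mean T1. The 2-hour label there, Section 8, and the Summary's description of readings before and 2 hours after the final-day dose all point to T1. That would settle the definition but leave the exposure mismatch.

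The protocol also never calls the comparison confirmatory. None of these points answers the difference in prior exposure.

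**Conclusion.** The point holds for one secondary objective. As designed, the pure-versus-cocoa comparison sets dosing after four weeks' supplementation against a single dose off supplement, so it cannot attribute a difference, or its absence, to source alone. With the protocol's effects of 1.5 and 1.3 points and an assumed overlap of 0 to 1, the artefact runs from 0 to −1.3 points (T1 to TA) or from +1.3 to 0 points (T0 to TA). At its extreme this is close to the assumed acute effect. It is a range of possible bias and not a prediction: it rests on equal true single-dose effects and on an overlap that the documents do not give. Two textual conflicts bear on the point and need reconciling: the exclusive positive-control role against the stated objective, and T0 against T1 as the reference for the acute change. The randomised Part 1 comparisons and the high-versus-low cocoa positive control are not affected by the mismatch.

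**What to change.** 1. Reconcile Section 1 and Section 3 (Part 1), which give cocoa a purely positive-control role, with the Summary, Section 2, Section 3 (Part 2) and Section 6.2.
2. Reconcile Section 3 (Part 1) with Section 8 so that the acute change is T1 to TA throughout. T0 to TA spans four weeks and mixes in the chronic effect.
3. Keep high versus low flavanol cocoa as the main Part 2 test.
4. Define the source comparison as [epicatechin minus placebo, T1 to TA] minus [high minus low flavanol cocoa, before to 2 h], in subjects who did both parts.
5. Report it with a confidence interval as exploratory and non-randomised. State that it compares dosing after four weeks' supplementation with a single dose, and that neither a difference nor its absence will be attributed to source alone.

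The cost is some wording, one within-person contrast and a weaker claim for one secondary objective. No dose, visit or measurement changes.
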